#### *Patient Education*

##### Medtronic SEEQ™ mobile cardiac telemetry system:

Given that a new adhesive sensor needs to be applied every 7.5 days, each subject in the intervention group will need to remove and re-apply a new sensor on 3 additional occasions. The first application will be done during hospitalization, under the supervision of the research coordinator. During the first sensor application, the subject will be educated on the appropriate use of this device, including the following:

- 1) Proper placement of the adhesive sensor.
- 2) Use and maintenance of the data transmitter.
- 3) Self-activation of the sensor for symptomatic episodes.

For subjects randomized to the intervention group, the research coordinator will contact them on a weekly basis by telephone to reinforce education of the proper use of the device (if necessary). In addition, adverse outcomes related to the use of the study interventional device will be assessed and an in-person clinic visit may be arranged if required.

Studies of the SEEQ™ mobile cardiac telemetry system had shown high levels of patient compliance and satisfaction with this device. In these studies, 98% of patients were able to properly apply the SEEQ™ adhesive sensor, patient compliance throughout the prescribed monitoring period was reported to be 90%, and 85% of patients were satisfied with the SEEQ™

mobile cardiac telemetry system. (<http://www.medtronicdiagnostics.com/us/cardiac-monitors/seeq-mct-system/evidence/index.htm>, accessed July 31 2015)

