#### **5.6.3 Additional 14-day cardiac rhythm monitoring at 6±1 months**

At the 6±1 month follow-up visit, all subjects (in the intervention group and the usual care group) will undergo 14 days of continuous cardiac rhythm monitoring with a wearable adhesive cardiac rhythm monitoring device. This will involve application of 2 SEEQ™ monitors over the

14-day monitoring period. As of October 1 2018, the CardioStat® device will replace the SEEQ™ mobile cardiac telemetry system. **5.7 Methods to Protect against Potential Bias**  
We have identified several potential sources of bias in this trial and have proposed methods to minimize them:

**Non-blinded study design:** SEARCH-AF is an open-label RCT since subjects and clinicians will be aware of the treatment assignment. Atrial arrhythmias detected by the SEEQ™ system will be initially interpreted by trained technicians in Medtronic's reading centre who are not involved in any part of the design and are unaware of the study design. Atrial arrhythmias detected by the CardioStat® cardiac rhythm monitoring system will be initially interpreted by trained technicians employed by Icentia Inc. who are not involved in any part of the study design. Adhering to standardized protocols, they are trained to interpret and report whether AF/AFL is present or absent and the duration of these episodes. We do not expect Medtronic or Icentia Inc. will play any role in biasing the results away from the null by preferentially "over-calling" AF/AFL episodes for participants in this study. In addition, full disclosure of the entire monitoring period can be retrieved. The generated rhythm strips and reports will then be sent to an independent group of adjudicators consisting of cardiologists and cardiac electrophysiologists. These adjudicators will over-read the reports with the attached rhythm strips and verify if the diagnosis is indeed correct. If needed, they will be able access full disclosure rhythm strips for further review. Additional rhythm monitoring with Holter, 12-ECG, in-patient telemetry strips, and cardiac event monitors will only be done on clinical grounds (ie: if deemed necessary by the treating physicians). Patient identification information will be removed and sent to the adjudicators for review, who will be blinded to the randomization status of the subjects. We believe these measures will minimize/mitigate potential bias due to the open-label design of SEARCH-AF.

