### **5.9 Proposed Frequency and Duration of Follow-up**

**Visit #1 (31-90 days after discharge):** All subjects will be assessed during follow-up at 31-90 days after discharge from their index cardiac surgery. Details of MACE and major bleeding events which occurred after hospital discharge will be recorded. As well, subjects' list of medications will be updated. Specifically, a detailed history of OAC use will be obtained, including the date of initiation, prescriber, dose, and type.

In this visit, subjects in the intervention group will return their data transmitters, have their wearable sensors removed (if still worn by the participant), and undergo a 12-lead ECG. Subjects in the control group will undergo a 12-lead ECG during this follow-up visit as well.

**Visit #2 ( $6\pm 1$  months after surgery):** Subjects will be assessed during a second follow-up visit at  $6\pm 1$  months after surgery. At this visit, all subjects will receive 14 days of continuous cardiac rhythm monitoring with a wearable adhesive cardiac monitoring device. All subjects will be educated on the proper use of the device. Details of MACE and bleeding events which occurred since the first follow-up visit will be recorded. As well, subjects' list of medications will be updated. A detailed history of OAC use will be obtained, including the date of initiation, prescriber, dose, type. At this visit, all subjects will undergo a 12-lead ECG.

**Visit #3 ( $9\pm 1$  months after surgery):** This visit will be conducted by telephone. At this visit, a history of OAC use will be obtained (type, dose, prescriber).

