### **2.2 Secondary Objectives**

To compare the following secondary outcomes between the enhanced cardiac rhythm monitoring group and the usual care group:

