#### **2.2.1 Secondary Outcomes**

- 1) Proportion of subjects with detection of cumulative AF/AFL lasting for  $\geq 24$  hours at the following time points:
  - i. within the first 30 days after randomization
  - ii. between day 31 and the last follow-up date
- 2) Duration of cumulative AF/AFL burden detected during the 14-day monitoring period (recorded by the wearable adhesive cardiac monitoring device) among subjects:

- i. between day 31 and the last follow-up date
- 3) Proportion of subjects who are prescribed oral anticoagulation at the following time points:
  - i. within the first 45 days after discharge from surgery
  - ii. between day 46 and the last follow-up date
- 4) Number of days during which the protocol-mandated wearable cardiac rhythm monitor sensor was worn by subjects.
  - i. within the first 30 days after randomization (note: applicable for enhanced cardiac monitoring group only)
  - ii. between day 31 and the last follow-up date
- 5) Reasons for premature removal of protocol-mandated wearable adhesive cardiac rhythm monitors by subjects.
- 6) Proportion of subjects who experienced adverse events related to the use of protocol-mandated wearable adhesive cardiac rhythm monitors at the following time points:
  - i. within the first 30 days after randomization
  - ii. between day 31 and the last follow-up date
- 7) Performance of non-protocol mandated Holter monitoring and/or event recorders during the 30-day period after randomization.
  - i. within the first 30 days after randomization
- 8) Proportion of subjects who experienced major adverse cardiac event (MACE) outcomes (ALL-cause death, myocardial infarction, ischemic stroke, non-CNS system embolism) at the following time points:
  - i. within the first 45 days after discharge from surgery
  - ii. between day 46 and the last follow-up date
- 9) Proportion of subjects with major bleeding events at the following time points:
  - i. within the first 45 days after discharge from surgery
  - ii. between day 46 and the last follow-up date
- 10) Hospitalization or emergency room visits.
  - i. within the first 45 days after hospital discharge from index cardiac surgery
  - ii. between day 46 and the last follow-up date

*(note: This secondary outcome was listed in the original clinicaltrials.gov submission dated on June 2 2016 but was not explicitly listed in the protocol).*

- 11) Proportion of subjects with cumulative AF/AFL lasting for  $\geq 6$  hours at the following time points:

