  - i. between day 31 and the last follow-up date
- 12) Histogram of compliance percentages (protocol-mandated wearable adhesive cardiac rhythm monitoring sensor use)
  - i. Within the first 30 days after randomization
  - ii. between day 31 and the last follow-up date
- 13) Daily burden of AF/AFL burden against time (Figure): This will be calculated on a per-subject basis.
  - i. within the first 30 days
  - ii. between day 31 and the last follow-up date
- 14) Cumulative burden of AF/AFL: this metric quantifies the percentage (%) of AF/AFL detected during time periods at which protocol-mandated continuous cardiac rhythm monitoring is performed (AF/AFL burden (%) = Cumulative duration of AF/AFL detected  $\div$  Total amount of time during which protocol-mandated cardiac rhythm monitoring was performed). This will be calculated on a per-subject basis.
  - i. within the first 30 days after randomization
  - ii. between day 31 and last follow-up date
- 15) Number of subjects who prematurely removed protocol-mandated adhesive cardiac rhythm monitoring sensors at the following time periods:
  - i. within the first 30 days after randomization
  - ii. between day 31 and the last follow-up date

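### Late AF/AFL burden is compared between arms as an absolute duration with no allowance for monitored time, although the SAP already defines a per-time percentage and leaves it descriptive

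*Supplement*

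**What the plan says.** SAP 2.2 introduces its list with "To compare the following secondary outcomes between the enhanced cardiac rhythm monitoring group and the usual care group". Item 2 of 2.2.1 is "Duration of cumulative AF/AFL burden detected during the 14-day monitoring period", for day 31 to last follow-up. It gives no unit, denominator, minimum wear or rule for a subject with no recording. SAP section 4 asks for an estimate, a 95% confidence interval and a p-value for every outcome comparison, so this will be an inferential result.

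The plan expects recording time to vary. Item 4 of 2.2.1 is "Number of days during which the protocol-mandated wearable cardiac rhythm monitor sensor was worn by subjects", and item 5 is "Reasons for premature removal of protocol-mandated wearable adhesive cardiac rhythm monitors by subjects". SAP 2.2.2 adds compliance histograms (item 12) and counts of early removals (item 15). Protocol v4.0, 5.14, accepts that subjects may stop wearing the device.

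SAP 2.2.2 item 14 defines a burden that allows for this: "this metric quantifies the percentage (%) of AF/AFL detected during time periods at which protocol-mandated continuous cardiac rhythm monitoring is performed". It is AF/AFL duration divided by monitored time, calculated per subject, for the late period as well. SAP 4.2 gives the outcomes in 2.2.2 descriptive summaries only.

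**The concern.** An absolute duration depends on how much AF a subject has and on how long the patch recorded. When the two arms' means are compared, any difference in mean wear enters the estimate as if it were a difference in AF. A difference in late wear is conceivable because only the intervention arm has worn patches before, for up to 30 days. At stake is the interpretation of one secondary outcome: a wear effect could be read as a change in late AF after early detection, or could hide one.

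Nothing else in the plan makes the allowance. SAP 4.2 names a chi-squared test for proportions and no method for a duration. The adjusted models in 4.3 are for binary outcomes, and wear is not among the candidate covariates. SAP 4.6 does not say whether a partial or absent recording counts as missing. Protocol 12.2 treats the remaining secondary outcomes as binary, so it supplies no method for this one either.

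**Working it through.** **The plan's own figure.** No sample size or effect size is stated for late burden. The only design figure is for the primary endpoint (protocol 12.1: 3% v 10%, 80% power, two-sided 0.05). With pooled variance and no continuity correction:

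n = [1.96√(2 × 0.065 × 0.935) + 0.8416√(0.03 × 0.97 + 0.10 × 0.90)]² / 0.07² = 193.5, so 194 per arm and 388 in total. 388 / 0.98 = 395.9, so 396.

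This reproduces the plan and does not depend on the present point.

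**Inputs for late burden.** From the documents: 14 days planned in both arms (protocol 5.9: "all subjects will receive 14 days of continuous cardiac rhythm monitoring with a wearable adhesive cardiac monitoring device"). Protocol 5.6.1 says of SEEQ that "patient compliance throughout the prescribed monitoring period was reported to be 90" per cent, which is not split by arm and not specific to the late period. All other wear times, AF fractions and prevalences below are assumptions.

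**One subject.** Expected duration = days worn × 24 × AF fraction. With an AF fraction of 10%:

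| Days recorded | Duration | Percentage burden |
|---|---|---|
| 14 | 33.6 h | 10% |
| 12.6 (90% of 14) | 30.24 h | 10% |
| 11 | 26.4 h | 10% |
| 10 | 24.0 h | 10% |
| 7 | 16.8 h | 10% |

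**Arm means with equal true AF.** The ratio of expected mean durations equals the ratio of mean wear, provided wear is unrelated to AF: 11/13 = 0.85 (15% lower), 12.6/14 = 0.90, 10/14 = 0.71, 7/14 = 0.50.

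In absolute terms the shift is small when AF is rare. Assume 10% of subjects have AF, with AF fraction Beta(0.5, 4), mean 0.5/4.5 = 0.111. Then:

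- 13 days: 0.10 × 0.111 × 13 × 24 = 3.47 h
- 11 days: 0.10 × 0.111 × 11 × 24 = 2.93 h
- difference: about 0.5 h

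**False-positive rate.** Simulated with identical AF in both arms, 194 per arm, the same Beta distribution, and every subject in an arm wearing the patch for the same time:

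| Wear (days) | AF prevalence | Welch, duration | Rank test, duration | Welch, percentage |
|---|---|---|---|---|
| 13 v 11 | 5–20% | about 4.5–7.5% | about 5% | – |
| 14 v 10 | 10% | 8.7% | 4.1% | 5.2% |
| 14 v 7 | 10% | 17.6% | 4.8% | 4.4% |
| 14 v 7 | 50% | 91% | 18.7% | 5.7% |

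In the 14 v 10 row the mean durations were 3.77 and 2.64 h, and the mean percentages 1.12 and 1.10. The last row is an extreme: half of all subjects in AF and half the wear in every subject of one arm. At low prevalence most subjects have zero burden, so a rank test barely sees the wear difference. The point estimate is affected in every row.

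**The case against.** The strongest reply is that the bias is hypothetical. Both arms have the same late plan: same visit, same 14 days, same device at any given date. The documents give no late wear by arm. Previous patch use could lower wear through fatigue or raise it through familiarity, since intervention subjects have already been trained. This stands: with equal mean wear there is no systematic error, only extra noise.

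A reader might also infer bias from the devices. Under protocol 5.6.3, "This will involve application of 2 SEEQ™ monitors over the" 14 days; at up to 7.5 days each they could record 15, against 14 for one CardioStat. But the device changed on a calendar date, and 1:1 allocation in permuted blocks stratified by centre balances the device mix in expectation. The 3.9% noise in protocol Appendix F comes from one sample report and says nothing about the arms. Neither supports a bias between arms.

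Misreading is partly guarded against. Late days worn is listed for comparison (2.2.1 item 4(ii)), and early removals, compliance and the percentage burden are reported (2.2.2 items 15, 12 and 14). A wear gap would be visible beside the duration result. That reduces the harm, but the estimate, interval and p-value would still belong to the quantity that mixes AF with wear.

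Finally, the protocol's own term in 5.12 item 2 is cumulative burden, which the SAP elsewhere defines as a percentage, so part of the conflict may be wording. Duration nevertheless reads naturally as absolute time, and two meanings for one term is a reason to settle it.

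**Conclusion.** The point holds as a minor one. The SAP compares a quantity that depends on monitored time while an exposure-adjusted version, already defined per subject for the same period, goes uncompared. If mean late wear differs by arm, the difference in mean duration is distorted in proportion: about 15% at 11 v 13 days, 10% at 12.6 v 14, 29% at 10 v 14. These wear times are assumptions.

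A reader might go further and conclude that the intervention arm will wear the patch less and so appear to have less late AF, or that the test is seriously invalid. The documents support neither: no difference in late wear is shown, its direction is unknown, and at low AF prevalence a gap of two days leaves the false-positive rate close to nominal. The primary analysis and sample size are untouched. The missing test and effect measure for this continuous outcome is a gap however wear turns out.

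**What to change.** In SAP 2.2.1 item 2:

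- Make the compared parameter the percentage burden of 2.2.2 item 14(ii), with the SAP's existing monitored-time denominator. Alternatively, model duration with monitored time as an offset.
- Name a test and effect measure suited to a continuous outcome with many zeros; for example, a difference in mean percentage burden with a bootstrap 95% confidence interval and a rank-based p-value.
- State that subjects with no late recording are missing, not zero, and fall under SAP 4.6.
- Keep absolute duration as a descriptive outcome.

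The cost is SAP wording. The percentage is already to be calculated for every subject, so no new data are needed.

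There are two drawbacks. The percentage is unstable when the recording is very short, which a sensitivity analysis can address. It also does not correct for wear that depends on AF itself, for example if subjects with symptoms keep the patch on longer. Items 1(ii) and 11(ii) of 2.2.1, the late 24-hour and 6-hour cumulative thresholds, depend on wear in the same way, so late days worn should be reported beside them.

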### **5.3 Clinical Events Committee (CEC)**

The Clinical Events Committee, composed of experts in the relevant fields, will review reported study clinical outcomes (arrhythmia, MACE events, and bleeding) to provide consistency and validity in the assessment of these outcomes. They will be blinded to treatment assignment when adjudicating such outcomes. In addition, this committee will be responsible for over-reading all rhythm strips, ECGs, full-disclosure Holter results, and full disclosure recordings from the wearable adhesive cardiac rhythm monitoring system (if necessary) to ascertain that AF/AFL was correctly diagnosed. A chairperson of the CEC will be nominated.

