## 5.12 Secondary Outcomes

- 1) AF/AFL lasting for  $\geq 24$  hours during 30 days after randomization and between day 31 and the last follow-up date.
- 2) Cumulative AF/AFL burden during the 14-day monitoring period (recorded by the wearable adhesive cardiac monitoring device) between day 31 and the last follow-up date.
- 3) Proportion of subjects who are prescribed with oral anticoagulation at the following timepoints: (i) 45 days after discharge from cardiac surgery; (ii) between day 46 and the last follow-up date.
- 4) Number of days during which the wearable adhesive cardiac rhythm monitor sensor was worn by subjects.
- 5) Reasons for premature removal of the wearable adhesive cardiac rhythm monitor by subjects.
- 6) Incidence of adverse events related to use of the wearable adhesive cardiac rhythm monitor.
- 7) Performance of non-protocol mandated Holter monitoring and/or event recorders during the 30-day period after randomization (for subjects in both groups).
- 8) Major adverse cardiac outcomes occurring within 45 days after hospital discharge, including the following: all-cause death, myocardial infarction, ischemic stroke, non-CNS systemic embolism (please refer to appendix H for endpoint definitions).
- 9) Proportion of subjects who experienced major bleeding events (please refer to appendix I for definitions of bleeding outcomes) within 45 days after discharge from cardiac surgery.

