## 5.13 Prescription of Oral Anticoagulation

It is possible that greater rates of AF/AFL detection in the early post-operative period may lead to increased prescription of oral anticoagulation by the subjects' treating physicians. The rates of OAC use between the intervention and control groups at 45 days,  $6\pm 1$  months, and  $9\pm 1$  months after discharge from cardiac surgery will be recorded as secondary outcomes. In addition, the type (and dosing if applicable) of OAC used will be collected. The choice of OAC that is prescribed will be at the discretion of the subjects' treating physicians and is not mandated by protocol.

In SEARCH-AF, the decision to initiate oral anticoagulation is not mandated by protocol but rather is left at the discretion of the subjects' treating physicians. The decision to treat a subject with OAC for AF-related stroke prevention after cardiac surgery is influenced by a number of factors including: (i) the subject's risk of stroke, (ii) the subject's risk of bleeding in the early post-operative phase, (iii) the subject's AF burden, (iv) the subject's treatment preferences. The relative weights of these factors will vary from subject to subject. Therefore, the decision to initiate OAC in this patient population is individualized.

At the current moment, there is no high-quality data to inform clinicians on the specific AF burden upon which OAC use will be beneficial in the post-cardiac surgical population. In the 2010 CCS AF guidelines, there was a conditional recommendation of low-quality evidence suggesting the use of OAC for post-cardiac surgical patients with continuous AF of  $>72$  hours [31]. Specifically, it emphasized an "individualized assessment of the risks of a thromboembolic

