## Appendix I: Bleeding outcome definitions

**Acute clinically overt bleeding** is defined as new onset, visible bleeding, signs, and/or symptoms suggestive of bleeding with confirmatory imaging techniques which can detect the presence of blood (e.g. ultrasound, computed tomography, magnetic resonance imaging)

The definition of **major bleeding** is adapted from the International Society on Thrombosis and Hemostasis (ISTH) definition.

**Major bleeding** is defined as a bleeding event which is:

- Acute clinically overt bleeding accompanied by one or more of the following:
  - A decrease in hemoglobin (Hgb) of 2 g/dL or more
  - A transfusion of 2 or more units of packed red blood cells
  - Bleeding that occurs in at least one of the following critical sites:
    - Intracranial
    - Intra-spinal
    - Intraocular (within the corpus of the eye; thus, a conjunctival bleed is not an intraocular bleed)
    - Pericardial
    - Intra-articular
    - Intramuscular with compartment syndrome
    - Retroperitoneal.
- Bleeding that is fatal.

**Clinically relevant non-major bleeding event:** The definition of clinical relevant non-major bleeding will be acute or sub-acute clinically overt bleeding that does not satisfy the criteria for major bleeding and that leads to one or more of the following:

- 1) hospital admission for bleeding.
- 2) physician-guided medical or surgical treatment for bleeding.
- 3) a change in antithrombotic therapy.

**Minor bleeding events:** All acute clinically overt bleeding events not meeting the criteria for either major bleeding or clinically relevant non-major bleeding will be classified as minor bleeding.

**Fatal bleeding event** is defined as a bleeding event that the adjudication committee determines to be the primary cause of death or contributes directly to death.

All acute clinically overt bleeding events will be adjudicated as a major bleeding event, or clinically relevant non-major bleeding event. Minor bleeding events will not be adjudicated.

[http://www.nejm.org/doi/suppl/10.1056/NEJMoa1107039/suppl\\_file/nejmoa1107039\\_protocol.pdf](http://www.nejm.org/doi/suppl/10.1056/NEJMoa1107039/suppl_file/nejmoa1107039_protocol.pdf) Accessed July 31 2015.

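### Protocol 5.9 and Appendix I disagree on which bleeds are recorded and adjudicated early after discharge, and the SAP reports clinically relevant non-major bleeding nowhere

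*Supplement*

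**What the plan says.** **Adjudication.** Protocol v4.0, Appendix I, defines major, clinically relevant non-major and minor bleeding. Of the middle class it says: "The definition of clinical relevant non-major bleeding will be acute or sub-acute clinically overt bleeding that does not satisfy the criteria for major bleeding", with admission, physician-guided treatment or a change in antithrombotic therapy as the qualifying consequences. It then states: "All acute clinically overt bleeding events will be adjudicated as a major bleeding event, or clinically relevant non-major bleeding event". Minor bleeds are exempt. Section 5.3 has the Clinical Events Committee review reported bleeding and adds: "They will be blinded to treatment assignment when adjudicating such outcomes".

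**Collection.** In section 5.9, Visit #1 (31 to 90 days after discharge) reads: "Details of MACE and major bleeding events which occurred after hospital discharge will be recorded". Visit #2 (6±1 months after surgery) reads: "Details of MACE and bleeding events which occurred since the first follow-up visit will be recorded".

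**Analysis.** SAP 2.2.1, item 9, is "Proportion of subjects with major bleeding events at the following time points", in two windows: the first 45 days after discharge, and day 46 to last follow-up. Protocol objective 5 (section 2.2) and outcome 9 (section 5.12) are also limited to major bleeding. None of the 15 descriptive outcomes in SAP 2.2.2 concerns bleeding.

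**Why bleeding is relevant.** Section 5.13 says it is possible that "greater rates of AF/AFL detection in the early post-operative period may lead to increased prescription of oral anticoagulation", and lists early post-operative bleeding risk among the factors in that decision.

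**The concern.** The trial is open-label, and bleeding is the natural counterweight to a gain in detection. Blinded adjudication protects the comparison only for events that reach the committee, and section 5.3 has it review what is reported. If Visit #1 passes on only bleeds the site already regards as major, the decisive classification is made by people who know the allocation. The documents do not show which way that would bias the comparison.

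Separately, the plan defines and adjudicates a second severity class and then has no place to report it. A bleed that led only to outpatient treatment or a change of antithrombotic therapy would appear in no SAP outcome as a bleed.

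**Working it through.** **1. The three instructions side by side (protocol v4.0)**

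| Place | Bleeds covered |
|---|---|
| Appendix I | Acute clinically overt bleeds, classed as major or clinically relevant non-major |
| 5.9, Visit #1 | Major bleeds only |
| 5.9, Visit #2 | Bleeding events, no severity limit |

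Visit #1 is narrower than both of the others. Appendix I also has a small internal gap: the non-major definition admits sub-acute bleeding, but the adjudication sentence covers acute bleeding only.

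**2. How much of the first window is affected.** Visit #1 covers the time from discharge. Held within its window, it falls on day 31 at the earliest, so its wording governs at least 31/45 = 69% of the first 45 days. It governs all of them if the visit is on day 45 or later. At most 45 − 31 = 14 days of that window come under the wider Visit #2 wording.

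**3. The plan's own size figure.** The only sample size in the documents is for AF/AFL detection (protocol 12.1): 3% v 10%, two-sided alpha 0.05, 80% power. With pooled variance and mean rate 0.065:

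n = [1.96·√(2·0.065·0.935) + 0.8416·√(0.03·0.97 + 0.10·0.90)]² / 0.07² = (0.683 + 0.290)² / 0.0049 ≈ 193.5, so 194 per arm.

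388/0.98 = 395.9, so 396 in total. This reproduces the plan exactly. No figure is stated for bleeding.

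**4. Size of the harm pathway.** Extra detections under the plan's assumptions: 0.07 × 198 = 13.9, about 14 subjects. The bleeding risks below are assumed, because the documents give none, and all 14 are taken as anticoagulated.
- Added major-bleed risk of 1% to 5%: 0.14 to 0.69 excess events.
- Added major-or-non-major risk of 10% to 20%: 1.4 to 2.8 excess events, or 0.7 to 1.4 points on 198.

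**5. Would the wider outcome be more informative?** The 95% half-width for the difference is 1.96·√(2p(1−p)/198), with the same assumed rate p in both arms. Power is for a doubling of p.

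| Assumed p | Events per arm | Half-width (points) | Power for a doubling |
|---|---|---|---|
| 1% | 2.0 | 1.96 | 13% |
| 2% | 4.0 | 2.76 | 21% |
| 3% | 5.9 | 3.36 | 30% |
| 5% | 9.9 | 4.29 | 47% |
| 8% | 15.8 | 5.34 | 69% |
| 10% | 19.8 | 5.91 | 80% |

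The rows from 5% up stand for a possible combined outcome. Their power figures mislead here. Doubling 8% or 10% needs about 16 or 20 excess bleeds, more than the 14 extra detections that could produce them. Against a plausible excess of 0.7 to 1.4 points, half-widths of 4.3 to 5.9 points are too wide. Adding the non-major class does not repair precision.

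**The case against.** Major bleeding is a legitimate, pre-specified outcome, named consistently in objective 5, outcome 9, Visit #1 and SAP item 9. A lower tier helps a committee sort cases, Appendix I takes its definitions from another trial's protocol, and nothing promises an analysis of the non-major class. That stands, so item 9 should stay as it is.

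There is partial cover elsewhere. Admissions and emergency visits are compared in SAP 2.2.1, item 10; admissions are generally serious adverse events under Appendix J; anticoagulant prescription is item 3. This also stands, but none of these identifies the event as a bleed, and bleeds managed without admission or an emergency visit fall outside item 10.

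The electronic case report form (v8.5.11, cited in SAP section 1) determines what Visit #1 captured, and it is not shown. The Visit #1 wording may be shorthand. A reader might infer that sites did filter bleeds; the documents support only that the text, followed literally, would have them do so.

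The non-major class has its own weakness. A change in antithrombotic therapy may be ascertained differently by arm in an open-label trial where anticoagulant use may differ. If Visit #1 used the narrower wording, early non-major events will also be incomplete. Both are reasons to report the class with its limits stated, not to omit it.

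**Conclusion.** The contradiction within protocol v4.0 is real, and it affects 69% to 100% of the first 45-day window if Visit #1 is held on time. The non-major class has no place in the SAP. The consequence is incomplete harm reporting, possibly filtered before blinded review. The primary analysis and every pre-specified outcome stand unchanged.

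Three stronger readings are tempting and not supported:
- That adding non-major bleeding would make the comparison adequately powered. Step 5 shows it would not.
- That major bleeding will certainly rest on a handful of events. No bleeding rate is given. Protocol 12.2, which takes the chi-square assumptions as not met for the remaining binary outcomes, points that way: under the usual rule of fewer than 5 expected per cell, that is a rate below about 5/198 = 2.5%. This is an inference.
- That a finding of no difference in bleeding would follow almost automatically. SAP sections 4 and 4.2 require an estimate with a 95% interval, so imprecision will be visible. A null on major bleeding should still not be read as absence of harm.

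The visit-window arithmetic and the textual comparison need no outside assumption; every bleeding rate used above is assumed.

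**What to change.** 1. **Protocol 5.9.** Reconcile Visit #1 with Visit #2 and Appendix I so that all clinically overt bleeds are recorded and sent to the committee without prior grading by the site. At the same time, settle whether sub-acute bleeds are adjudicated.
2. **SAP.** Keep item 9 unchanged. Add to 2.2.2, as a descriptive safety outcome, committee-adjudicated clinically relevant non-major bleeding, and major or clinically relevant non-major bleeding, by arm in the same two windows, with risk difference and 95% interval. SAP 4.2 gives 2.2.2 outcomes only descriptive summaries, so the new line should state that it carries an interval and no test.
3. **Stated limits.** Say that events before Visit #1 may be incomplete if the narrower wording was used, and that the change-of-therapy component may be ascertained differently between arms. Check the case report form to establish what was asked.

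The cost is an aligned phrase in 5.9, one SAP line and a few table rows, with no new visits or procedures. If Visit #1 is already complete, only the adjudicated events to hand can be reported. The downside is one more outcome, with weaker early ascertainment than major bleeding. The SAP has already added items 10 and 11, which its notes say the protocol does not explicitly list, so an addition of this kind has precedent.
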